### Study procedures

Following contact with the research team, potential participants will be telephone screened for inclusion and exclusion criteria. Participants will then undergo a physical assessment at Deakin University to confirm diagnosis of PFP and the exclusion of other diagnoses of knee pain (e.g., Osgood Schlatter’s disease). All screening procedures will be performed by a registered podiatrist (NM) with more than nine years of clinical practice experience who has undergone additional training in PFP diagnosis by an experienced physiotherapist (JB).

Eligible participants will provide written consent to participate along with their parent or guardian for those under 18 years of age. Following baseline data collection eligible participants will be randomised to receive either (i) a flat, flexible school shoe, or (ii) a traditional school shoe to be worn throughout the 12-week study period. Randomisation procedures will be performed by a researcher external to this project.

As the outcomes within this study are patient reported, this study is considered assessor-blinded which is consistent with other RCTs utilising footwear interventions [39]. The research team processing the participant-reported data will be blinded to group allocation. Due to the inability to blind participants to the shoe they are wearing, participants will not be informed of the hypotheses of the study, nor of the differences between the shoes [39]. They will simply be recommended to wear the shoe at all times they would usually wear their school shoe. Participants will be able to keep their allocated shoe at the cessation of the trial. Participant flow through the study is outlined in Fig. 1.

**Fig. 1 Fig1:**
[figure not shown]
Participant flow through the study

### Randomisation

Randomisation procedures will be performed via fixed concealed allocation. The randomisation sequence will be computer generated with permuted blocks of four or six participants. All assessors responsible for measuring and analysing key outcomes will be blinded to participant allocation.

### Interventions

Participants will be fitted into both types of footwear at baseline by a podiatrist (NM) with nine years of clinical and footwear fitting experience to ensure they are comfortable and correctly fitted [41]. At this time, participants will be issued with an information sheet (see Additional file 1) outlining important information about their shoes, the study, and the requirements of participation within the study. Participants will be advised to wear their allocated shoe for the duration of time per week they would normally wear their school footwear.

#### Flat, flexible school shoe

Participants randomised to flat, flexible school shoes will receive the Vivobarefoot Primus Lite and/or the Vivobarefoot RA II (Fig. 2), which are both commercially available flat, flexible black lace up shoes (Vivobarefoot, Freiburg, Germany). The Primus Lite and the RA II are lightweight, have a 3 mm outsole, zero heel-toe offset, a mass of 180 g, and no stability or motion control features. The Primus Lite and the RA II score 25/25 on the minimalist shoe index [42]. Participants will receive either the RA II or the Primus Lite dependant on shoe size and stock availability. Participants will wear this shoe as per school requirements throughout the 12-week intervention period.

**Fig. 2 Fig2:**

Flat, flexible footwear to be used within study, Vivobarefoot Primus Lite (left) & Vivobarefoot RA II (right) (Vivobarefoot, Freiburg, Germany)

#### Traditional school shoe

Participants randomised to the traditional school shoe will receive a pair of Clarks Daytona (Fig. 3) (Clarks, Street, England). The Clarks Daytona has a stiff midsole and heel counter, a 12 mm heel-toe offset, and mass of 350 g. The Clarks Daytona scores 2/25 on the minimalist shoe index indicating a low degree of minimalism and flexibility [42].

**Fig. 3 Fig3:**
[figure not shown]
Traditional school shoe to be used within study, Clarks Daytona (Clarks, Street, England)

### Concomitant care

If participants are taking medication for their knee pain, they will be permitted to continue this throughout the study duration. This is consistent with other studies performed in adolescents with PFP [13, 37]. At the time of entry within the study, participants will be asked to refrain from commencing new treatments for their knee pain for the duration of the study and to avoid using other assistive devices such as braces or orthotics for the study duration. Participants will be asked to report any use of co-interventions in the weekly log sheet (see Additional file 2).

### Outcome assessment

Once consent is provided, baseline testing will follow at the Deakin University 3D Gait Laboratory. The duration of testing will be approximately 1.5 h. Baseline information will be obtained from participants including demographic data, body mass and height, sex, affected knee/s, duration of symptoms, previous treatments, and aggravating activities [43]. To assess the stage of adolescence, participants will complete the modified Pubertal Maturational Observational Scale at baseline [44]. This scale has been used in other studies involving adolescents and can be used to reliably classify adolescent developmental stages [45–47].

Participants will complete self-reported outcome measures at baseline, six weeks, and 12 weeks. Data collection will be performed through self-reported questionnaires performed via Qualtrics™ (Qualtrics, Provo, United States of America). Throughout the duration of the study participants will be asked to keep a weekly log (see Additional file 2) of the type of shoe worn that day; hours spent wearing that shoe; any adverse events associated with the allocated school shoe; use of co-interventions (e.g., pain medication, other footwear, taping); and any other comments. Participants will complete this in an online format distributed to them weekly via Qualtrics™. If participants do not have the equipment required to access the online format, a hard copy will be provided.

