### Adverse events

For the study duration participants will be advised to report information on adverse events and/or use of concomitant care within their weekly log sheet. Participants will be encouraged to report any discomfort they experience to the research team. If required, participants will attend an additional appointment with the research team to discuss any discomfort they may be experiencing. In this instance, standard clinical practice principles will be applied. The researcher may recommend strategies to improve the adaptation (e.g. a return to their regular footwear until pain settles). These events will be recorded as adverse events and if the discomfort cannot be reduced or tolerated, the participant will be encouraged to return to using their normal footwear and the individual’s participation with the intervention will be ceased.

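### The weekly log, as described, limits its adverse event item to shoe-related events, while the Adverse events section sets no such limit; the two should be reconciled and the item made cause-neutral

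*Protocol article*

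**What the plan says.** The protocol article describes the reporting of adverse events in two places.

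- **Outcome assessment** lists the contents of the weekly log. The adverse event item is "any adverse events associated with the allocated school shoe". The log also covers shoe type, hours of wear and co-interventions, and ends with a free field, "and any other comments". The participant fills it in: "Participants will complete this in an online format distributed to them weekly via Qualtrics".
- **Adverse events** says that "participants will be advised to report information on adverse events and/or use of concomitant care within their weekly log sheet". Attribution to the shoe is not a condition. A second route follows: "Participants will be encouraged to report any discomfort they experience to the research team". An extra appointment is offered if needed, and of discomfort handled in this way the section says "These events will be recorded as adverse events".

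On blinding, Study procedures says: "Due to the inability to blind participants to the shoe they are wearing, participants will not be informed of the hypotheses of the study". The same sentence adds that they are not told how the shoes differ.

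The log form itself is Additional file 2, which is not among the documents at hand.

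**The concern.** An item limited to events associated with the shoe makes the participant judge causation before anything is recorded. Here that judge is an adolescent who knows the allocation. An event that the participant does not link to the shoe falls outside the item, and the threshold for making that link may differ between arms.

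A difference between arms is plausible on the document's own facts. Exclusion (v) under Participants removes adolescents who already wear flat, flexible shoes to school, so that shoe is new as school wear to everyone. The Background describes usual school footwear in terms closer to the traditional shoe. Participants are also fitted into both shoes at baseline, and walk and run in both, so they feel the contrast even though nobody explains it.

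At stake is the quality of the adverse event record in a trial meant to show what a larger trial will need. The Discussion says the clinical effects of this footwear in adolescents are unknown, and the safety evidence it cites comes from adults. If the restricted item is carried forward, the weakness goes into the main trial with it.

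**Working it through.** The plan gives no figure for adverse events. Its one computed figure, the minimum of 23 participants, concerns adherence and does not bear on this point. The check is therefore mainly a comparison of the text.

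**Step 1: the routes side by side.**

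| Route | Section | Asked every week? | Limited to the shoe? |
|---|---|---|---|
| Adverse event item in the log | Outcome assessment | Yes | Yes |
| Adverse events in the log | Adverse events | Same log | No |
| Comments field in the log | Outcome assessment | Yes, but does not ask about health | No |
| Discomfort told to the team | Adverse events | No, participant-initiated | Not by its wording; the follow-up concerns adapting to the shoe |

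The first two rows describe the same log with different scope. The last two are open to any event, but neither is a systematic question about health put each week to both arms.

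**Step 2: which events are exposed.** Knee symptoms are also measured without attribution: worst and usual pain on the VAS, KOOS-Child, KOOS-PF and AKPS at baseline, 6 and 12 weeks. The global rating of change at 6 and 12 weeks asks how knee pain has changed, not why. A lasting worsening at the knee would show there. What remains exposed is mainly symptoms elsewhere, such as the foot or calf, together with knee flares that come and go between assessments.

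**Step 3: how the filter would act (illustration; all rates assumed).** Let *t* be the true event rate, equal in both arms, and let *a₁* and *a₀* be the proportions of events attributed to the shoe in the flat and traditional arms. Suppose the restricted item were the sole route. The apparent ratio would be

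(t × a₁) / (t × a₀) = a₁ / a₀.

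The true rate cancels. With 12 per arm (assumed equal split of 24) and t = 30%, 12 × 0.30 = 3.6 events are expected in each arm:

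| a₁ | a₀ | Logged, flat | Logged, traditional | Apparent ratio |
|---|---|---|---|---|
| 50% | 50% | 1.8 | 1.8 | 1.0 |
| 60% | 50% | 2.2 | 1.8 | 1.2 |
| 80% | 40% | 2.9 | 1.4 | 2.0 |
| 90% | 30% | 3.2 | 1.1 | 3.0 |

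Equal attribution leaves the ratio at 1.0 but halves the count in the first row. The table shows the mechanism and does not estimate its size: nothing in the documents favours one row over another, and the other routes in step 1 would weaken the effect.

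**The case against.** The case on the other side is substantial.

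- **The form is not shown.** Outcome assessment gives a one-sentence summary of the log, and the form may already ask about any event. This stands. The finding concerns how the article describes the log, and bias is a risk rather than an established fact.
- **The Adverse events section is the dedicated one, and it is broader.** It sets no attribution limit and adds the discomfort route; the comments field is open too. This stands against any claim that shoe-related events are all that can be captured. A reader might infer that unattributed events are lost in both arms, or that the total rate can never be recovered. The documents do not support either reading, because these routes exist. They do not remove the inconsistency, however, or replace a weekly question that asks about health irrespective of cause.
- **Knee outcomes are collected regardless of attribution.** This stands, and narrows the concern mainly to symptoms away from the knee.
- **Withholding the hypotheses and the shoe differences lessens unequal attribution, and both arms receive a study shoe.** This stands in part. The participant still makes the causal judgement, and the flat shoe is still the less familiar type.
- **No between-arm safety comparison is planned.** This stands. Adverse events are neither a feasibility criterion nor a listed secondary outcome, and the planned analysis is descriptive.

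**Conclusion.** The two sections describe the scope of adverse event reporting differently and should be reconciled. As described under Outcome assessment, the log item puts a causal judgement by unblinded participants ahead of the record. It may undercount events, mainly away from the knee, and may do so to a different degree in each arm.

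The size is unknown. A reader might infer a two- or three-fold spurious excess in the flat-shoe arm from the illustration. That does not follow, since those ratios come wholly from assumed attribution rates and from treating the item as the sole route.

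Severity is modest. None of the three feasibility criteria is a safety criterion, and the results are descriptive in 24 participants. There is an indirect link to those criteria: discomfort that cannot be settled or tolerated ends the participant's use of the allocated shoe, which can affect adherence and possibly dropout. The main reason to act is that the trial is meant to inform a larger one. The conclusion assumes that the log form matches its description in the article.

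**What to change.** Check the log form against both sections and make all three agree. Have the log ask both arms, in identical words every week, for any new or worsened symptom, injury or health problem, whatever its cause. Follow it with a separate question on whether the participant thinks the shoe was involved. Tabulate all events by arm first and shoe-related events second.

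The cost is a small change to the log, an ethics notification and slightly more events to tabulate. If the form already asks for events irrespective of cause, correcting the description under Outcome assessment and adding the relatedness question, if it is absent, would be enough.

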### Outcomes measures

#### Primary outcome measures

The primary outcome from this study is to determine the feasibility of conducting a full-scale RCT in adolescents with PFP. Feasibility will be assessed by the following outcome parameters; (i) adherence to allocated shoe wear of ≥ 75% of their total weekly school shoe wear time, (ii) a recruitment rate of one participant per fortnight, and (iii) a dropout rate of ≤ 20%. Success of blinding and participants’ expectations of treatment will be evaluated using the Credibility and Expectancy Questionnaire [48]. This will be completed at the end of the baseline assessment immediately after participants have been fitted into their shoes and then at the end of week one [37].

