### Participants

Male and female adolescents will be eligible for inclusion if they meet the following criteria: (i) aged between 12–18 years, (ii) have PFP from a non-traumatic onset of at least six weeks duration, (iii) have pain ≥ 30/100 mm (mm) on a visual analogue scale (VAS), and (iv) have knee pain which is aggravated by activities that load the patellofemoral joint (e.g., squatting, stair ascent or descent, running).

Adolescents will be excluded if they (i) have pain at sites other than the anterior knee (e.g., other knee structures, hip, pelvis, lumbar spine), (ii) have a history of hip, knee or spine surgery, or other suspected knee joint pathology (e.g., Sinding Larsen Syndrome, Osgood Schlatter’s Disease), (iii) have planned lower limb surgery, (iv) have a neurological condition or systemic arthritis, (v) are currently wearing flat flexible footwear for school and/or (vi) have any condition which prevents them from wearing flat flexible footwear (e.g., calcaneal apophysitis).

Adolescent volunteers will be recruited from the community using a targeted comprehensive recruitment strategy with proven efficacy in previous studies of PFP [28, 37, 38]. Recruitment strategies will include paid social media advertising, dissemination through social media networks and flyers displayed at local sports medicine and allied healthcare clinics, footwear stores and sporting clubs/recreational facilities where PFP is likely to be prevalent. Eligibility criteria are based on previous high quality RCTs for PFP [13, 37].

To observe feasibility outcome of adherence, we plan to recruit 24 participants with PFP. A minimum of 23 participants are required to observe the feasibility outcome of adherence ≥ 75% allocated shoe wear indicating progression to a full trial is feasible. If adherence to allocated shoe wear is ≤ 50% (i.e., two school days per week, excluding a sporting day) progression to a main trial is not feasible (alpha < 0.05, β 0.2) [37, 39, 40].

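### The adherence criterion names no arm and its sample size counts both, so wear of the traditional shoe can mask flat-shoe wear at the plan's own stop level

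*Protocol article*

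**What the plan says.** In the protocol article, *Primary outcome measures* sets the first feasibility parameter: "Feasibility will be assessed by the following outcome parameters; (i) adherence to allocated shoe wear of" at least 75% of total weekly school shoe wear time. No arm is named. *Interventions* issues an allocated shoe to every participant, flat and flexible in one arm and traditional in the other, and gives both arms the same instruction: "Participants will be advised to wear their allocated shoe for the duration of time per week they would normally wear their school footwear".

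The final paragraph of *Participants* makes adherence the basis of the sample size: "To observe feasibility outcome of adherence, we plan to recruit 24 participants with PFP". It continues: "A minimum of 23 participants are required to observe the feasibility outcome of adherence" of at least 75%, the level described as "allocated shoe wear indicating progression to a full trial is feasible". At 50% or below the outcome is stop: "i.e., two school days per week, excluding a sporting day) progression to a main trial is not feasible". The error rates are given as "alpha < 0.05, β 0.2". *Planned statistical analysis* says that the feasibility outcomes will be described against the pre-specified criteria. It does not say whether that is done by arm or overall.

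**The concern.** The main unknown for the future trial is whether adolescents will wear a flat, flexible shoe to school. *Background* offers better adherence than exercise therapy as a reason for studying the shoe. The control arm receives a traditional school shoe, and people who already wear flat, flexible school shoes are excluded. Control wear is therefore likely to be close to usual behaviour, and it carries little information about wear of the new shoe.

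If one adherence figure covers both arms, high control wear offsets low flat-shoe wear. The plan could then report its main progression criterion as met, or at least well clear of stop, while the flat shoe is worn at the level the plan itself calls not feasible. Adherence is the only criterion with separate go and stop levels, and it is the only basis given for the sample size.

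**Working it through.** **Inputs from the article.** Planned total 24; minimum 23; go level p1 = 0.75; stop level p0 = 0.50; alpha 0.05; beta 0.2; two parallel groups.

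**Assumptions.** Equal allocation, 12 per arm (the ratio is not stated). Control adherence of 85% to 100% (the article gives no figure). For steps 2, 3 and 5, adherence is yes/no per participant and a pass is an observed 75%, that is 18/24 pooled or 9/12 in one arm.

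**Step 1: reproduce the 23.** One-sample proportion, normal approximation:

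n = [(z_alpha·√(p0·q0) + z_power·√(p1·q1)) / (p1 − p0)]²

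One-sided: [(1.645 × 0.5 + 0.842 × 0.433) / 0.25]² = 22.54, rounded up to 23. An exact check with at least 16/23 as the rule gives alpha 0.047 and power 0.804. The two-sided version gives 29, and a two-arm comparison of 0.50 with 0.75 would need 46 (one-sided) or 58 (two-sided) per arm. So 23 is a single-group figure, and with 24 randomised to two arms only the combined sample can supply it.

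**Step 2: chance of a pooled pass with the flat shoe at the stop level.** Let F ~ Bin(12, 0.50) be the number adherent in the flat arm and C ~ Bin(12, pC) the number in the control arm. P(F + C ≥ 18) comes from exact convolution, as does the chance of landing at or below the 50% stop level, P(F + C ≤ 12).

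| Control adherence pC (assumed) | Expected pooled | P(≥18/24) | P(≤12/24) |
|---|---|---|---|
| 85% | 67.5% | 0.27 | 0.043 |
| 90% | 70.0% | 0.37 | 0.018 |
| 95% | 72.5% | 0.48 | 0.005 |
| 100% | 75.0% | 0.61 | 0.0002 |

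**Step 3: reference case.** If both arms were truly at 50%, P(≥18/24) would be 0.011.

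**Step 4: the same question on mean wear time.** With equal arms the pooled mean is the average of the two arm means. Flat 50% with control 90% gives (50 + 90)/2 = 70%; with 95%, 72.5%; with 100%, 75%. With the flat arm at 50%, the threshold is reached only at 100% control wear. In every case the pooled mean is well above 50%.

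**Step 5: what the flat arm alone can support.** With 12 participants and a rule of at least 9/12, P(pass) = 0.073 when true adherence is 50% and 0.649 when it is 75%. The exact (Clopper-Pearson) 95% interval for 9/12 is 43% to 95%. An exact one-sided 0.05 test in 12 needs 10/12, with alpha 0.019 and power 0.39.

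**The case against.** **Pooling is not stated.** This is true. The article does not say that the arms are combined, and a full protocol or analysis plan may tabulate adherence by arm. But the article itself defines the criterion, the go and stop levels and the number needed, and that number works only across both arms. Tables by arm would not settle which figure decides progression. If a per-arm rule was meant, the stated error rates do not hold for it. Either way the text needs correcting.

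**The plan's own scale is wear time.** The stop level is glossed as days of wear and the go level as a share of weekly wear time, so the yes/no probabilities rest on a change of scale. That stands as a qualification. The yes/no reading has support because 23 reproduces as a proportion test. A reader might infer that near-ceiling control wear is enough for a pass whenever the flat shoe is at 50%. On mean wear time that is wrong: 95% control wear leaves the pooled figure at 72.5%, a miss. What survives on that scale is that the figure stays far from stop.

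**Control adherence is assumed.** It is. Controls must wear a newly issued model, so near-ceiling wear is plausible but not documented. That is why the range runs down to 85%, and at 95% or below the pooled rule fails more often than it passes.

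**Control adherence matters too.** It does, because the future trial compares two arms. A reader might infer that control wear is uninformative and can be set aside. The article's objective, feasibility of the whole trial, does not support that. It is a reason to report each arm against the threshold.

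**Other safeguards exist.** Recruitment and dropout are also criteria, and the weekly log would show poor flat-shoe wear. Neither changes what the adherence criterion would report.

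**Conclusion.** The concern holds in a limited form. The adherence criterion names no arm, and its sample-size basis makes it pooled in effect. With flat-shoe adherence at the plan's 50% stop level, the pooled criterion would be met with probability 0.27 to 0.61 for control adherence of 85% to 100%, against 0.011 if both arms were at 50%, and the stop level would be reached less than 5% of the time. These figures assume 12 per arm and yes/no adherence per participant. On mean wear time a pass requires 100% control wear, and the main effect is that the stop rule would not be expected to fire.

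The documents do not support saying that the plan explicitly pools the arms, or that a false go is certain or even likely across the whole range. They do support saying that the rule as written cannot separate an unworn flat shoe from moderate wear in both arms.

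**What to change.** In *Primary outcome measures* and *Planned statistical analysis*, state that the adherence criterion is applied by arm and that progression requires the flat, flexible arm to meet it. Report the traditional-shoe arm against the same threshold, and give the pooled figure as description only.

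In *Participants*, say that the stated alpha and 80% power refer to the pooled 23 to 24 participants and not to either arm. Give the precision for 12: a 9/12 rule has a 7.3% chance of a false go at 50% and a 65% chance of go at 75%, and an observed 9/12 has an exact 95% interval of 43% to 95%.

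The cost is a few sentences and a less favourable statement of precision. No new data are needed, because the weekly log already records the shoe worn and the hours. No extra enrolment is needed either, provided the team accepts the weaker error rates. Keeping the stated rates within the flat arm would take 23 in that arm, about 46 in total at equal allocation.
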